**Discussion:**

This study is a unique dyadic intervention focused on both girls and their mothers or female caregivers to drive cervical cancer control in Africa. Findings have the potential to inform local and global policies aimed at reducing the cervical cancer burden in African countries like Nigeria, eliminating missed opportunities by closing the research-to-translation gap. The protocol was registered with clinicaltrials.gov under registration NCT06728085.

**Supplementary Information:**

The online version contains supplementary material available at 10.1186/s13012-025-01428-5.

Contributions to the literatureThe study will be the first study to test whether a combined mother-daughter HPV campaign, tailored to local contexts, with education on cervical cancer and onsite services provided (i.e. access to HPV vaccination and screening in private spaces), increases HPV vaccination among daughters and HPV self-collection among mothers recruited in Nigeria.This is the first application of crowdsourcing and participatory approaches to optimize cervical cancer control among mother-daughter dyads in Nigeria.Our study is designed to provide decision-makers with evidence, including the cost-effectiveness of a final combined implementation strategy bundle for HPV vaccination and screening among mother-daughter dyads in Nigeria.

## Introduction

Eliminating invasive cervical cancer in African countries is a challenge. In 2022, there were 13,676 new cervical cancer cases and 7,093 associated deaths in Nigeria, making cervical cancer the second most common cancer in women [1]. Cervical cancer is caused by persistent infection with one of 13 carcinogenic human papillomavirus (HPV) types [2]. The World Health Organization has called for the global elimination of cervical cancer to achieve 90–70–90 targets by 2030, whereby 90% of girls are fully vaccinated for HPV by age 15, 70% of women are screened with high-performance tests by the age of 35 years and again by age 45, and 90% of women with cervical pre-cancer or cancer are treated [2, 3]. Multiple evidence-based strategies for promoting HPV-based prevention methods have been developed, including strategies targeting health, school, family, community, and policy contexts [4–6]. Yet barriers to the uptake of these methods exist at multiple levels, including individual (low-risk perception levels), dyadic/social (poor support), and community/structural (limited [6]access) systems [7–10]. HPV vaccination of girls and HPV self-collection for cervical cancer screening among mothers (or caregivers, guardians), particularly mother/daughter dyads within family and community systems, may be able to overcome some of these barriers [11–16]. However, both vaccination and HPV self-collection services are still largely inaccessible and have limited input from end-users, especially local girls and their mothers. Nigeria is unlikely to eliminate cervical cancer unless HPV prevention methods are tailored and implemented in culturally compelling, cost-effective and sustainable ways [3]. One approach to expanding the implementation of HPV prevention strategies is crowdsourcing.

Crowdsourcing has a group collectively solve a problem and then implement proposed solutions [17]. This encompasses various participatory activities, including open calls to obtain ideas, designathons, and participatory learning communities [18, 19]. Learning community groups are structured, collective, problem-solving, participatory strategies that convene participants around a common problem, working together to learn best practices and exchange experiences informed by quality improvement methods [20]. Crowdsourced implementation strategies can expand the acceptability, feasibility, and sustainability of HPV-prevention methods by leveraging end-user expertise directly to design and implement evidence-based strategies relevant to the local context [21, 22]. Researchers, community members, and other relevant actors work together to learn from each other, generate knowledge, and support change in a participatory manner [23]. These participatory strategies also advance health equity by centering relationships between researchers and those with lived experience to improve the pathway between research and practice necessary for eliminating persistent inequities in health [24]. Crowdsourcing approaches have been used before in Nigeria to increase HIV and STI test uptake among Nigerian youth [21].

Nigeria has programs and infrastructure in place to support the combined implementation of HPV vaccination and HPV self-collection among mother-daughter dyads [3]. Recently, to immunize 16 million girls by 2025 with a single dose of HPV vaccine, Nigeria launched a nationwide rollout of HPV vaccination in October 2023 when 15 states plus the Federal Capital made HPV vaccination available to approximately 5.3 million girls in an initial phase [25]. Phase 2 launched in May 2024 and over seven million girls in 21 states were vaccinated [25]. HPV vaccination is classified as a best buy for non-communicable diseases and is considered a highly cost-effective and affordable intervention for cervical cancer prevention [26]. Likewise, the 2019 Nigerian Society of Obstetrics and Gynecology guidelines [27], as well as the Nigerian National Strategic Plan for cancer, recommend routine HPV screening for women by ages 30–65 years old, including the early detection of asymptomatic pre-cancerous lesions and prompt treatment to prevent cervical cancers [3, 28]. Nonetheless, attempts to implement HPV vaccination and HPV screening in real-world settings in Nigeria have focused on standalone interventions implemented separately with girls or women as with the national rollout of HPV vaccination. Few studies have investigated the strategies necessary to integrate both HPV vaccination and HPV screening with mother-daughter dyads simultaneously, despite the availability of evidence suggesting its feasibility [16, 29]. Combined HPV vaccination and screening have the potential to improve the adoption of cervical cancer prevention interventions [16]. Such an approach capitalizes on reciprocal learning between mothers and daughters and facilitates the mutual reinforcement of health prevention practices and behaviors [12, 30–32]. Notably, dyadic approaches align with many cultures where parents make important health decisions for young girls [33–35]. Given the high incidence and mortality rates of cervical cancer in Nigeria, efforts to equitably increase the uptake of HPV vaccination and HPV screening using culturally compelling strategies are needed.

Known locally as the For Girls and Women (4GW) study, the study builds on our team’s participatory implementation science research for HIV prevention in Nigeria [36]. We organized a participatory HIV research study called 4 Youth by Youth study [22]. In the pre-implementation phase (Years 1–2), we conducted a crowdsourcing open call and used designathons and innovation bootcamps (similar to our HIV research) to develop implementation strategies for increasing HPV vaccination and HPV screening among mother-daughter dyads [37]. We iteratively piloted and refined the strategies using participatory learning communities and created and finalized study materials similar to our prior research [21]. Preliminary findings demonstrate that an implementation strategy [38] bundle that combines a mother-daughter campaign, tailored and adapted to local contexts, with education on cervical cancer and access to onsite services (i.e. access to HPV vaccination and HPV screening in private spaces) that engages mothers and daughters as an implementation strategy bundle, increases the uptake of HPV vaccination among Nigerian girls and HPV screening among their mothers. Here, we describe the study protocol for the stepped-wedge cluster randomized control hybrid type II trial to be implemented by trained community health workers (CHWs) in 18 local government areas (LGAs) with 612 mother/daughter dyads. The purpose of the trial is to evaluate the effectiveness and cost-effectiveness of the final combined implementation strategy bundle for HPV vaccination and screening among mother/daughter dyads in Nigeria.

## Methods

This study is a collaboration between the Washington University School of Medicine, the University of North Carolina at Chapel Hill, Monash University, Wake Forest University School of Medicine, and the Nigerian Institute of Medical Research (NIMR). Established in 1977 as Nigeria's premier national medical research institute under the Ministry of Health, NIMR is a hub for research, capacity building, and collaborative efforts to advance national development. Its mission encompasses basic, applied, and implementation science research on infectious and non-communicable diseases of public health relevance in Nigeria. This work is funded by the National Cancer Institute, with pre-implementation and implementation phases focused on collaborative, community-engaged strategies for cervical cancer and HPV prevention.

This hybrid effectiveness type II [39] stepped-wedge cluster randomized trial will test the hypothesis that a combined mother-daughter campaign, tailored and adapted to local contexts, with education on cervical cancer and onsite services provided (i.e. access to HPV vaccination and screening in private spaces), increases HPV vaccination among girls and HPV self-collection among mothers. This study was conducted and reported in accordance with the CONSORT extension for Stepped-Wedge Cluster Randomized Trials (SW-CRTs) to ensure transparency, completeness, and methodological rigor [40]. The CONSORT extension provides specific guidelines for reporting SW-CRTs, including the justification for the use of the stepped-wedge design, details of the cluster randomization process, sequence generation, and allocation concealment. (See Supplementary File 1 for the CONSORT checklist).

Mothers are female caregivers such as biological mothers, aunts, grandmothers, or guardians. We selected a pragmatic type II hybrid effectiveness design because it allows for a simultaneous assessment of the intervention implementation effectiveness and clinical outcomes assessment [39]. The study will be conducted among 612 mother-daughter dyads (*n* = 612 × 2 = 1,224 participants) recruited from 18 LGAs to a stepped-wedge randomized control trial of the crowdsourced intervention versus usual care. All mother-daughter dyads will be followed for 12 months. The Proctor’s Implementation Outcomes Framework [41] and the PEN- 3 cultural model [42] will guide the analysis and evaluation of the implementation process. We will recruit and train one CHW per LGA (*n* = 18) with one supervisor per LGA (n = 18) to assist with overall study implementation. Before participant recruitment, all CHWs will receive training on the final intervention, good clinical practice and human subject research. CHWs are key partners [43] that will recruit mother-daughter dyads meeting the eligibility criteria, identify barriers to engagement and participation, tailor and adapt the mother-daughter campaign to include access to onsite services for HPV self-collection kits, screen mothers and vaccination of girls by study nurses. CHWs will transport self-collected cervical samples to the NIMR laboratory, provide test results, link mothers to treatment for positive test results and retain participants overtime to advance efforts to eliminate cervical cancer in their LGAs. The trial is designed as a pragmatic study to closely mirror real-world conditions for on-going HPV prevention services in Nigeria.

### Conceptual framework

The study design, methods, and analysis integrate implementation science frameworks, specifically Proctor’s implementation framework [41], with a community-engaged approach informed by the PEN- 3 cultural model [42] and social learning principles [44, 45]. The PEN- 3 focuses on Perceptions (beliefs), Enablers (resources), and Nurturers (peers, family, community support) impacting health within a cultural context considering the Positive, Existential and Negative factors [46]. It has been used to explore health needs and research questions, determine study design, recruit participants, and implement and disseminate health research findings congruent with participant beliefs and perceptions [46]. Researchers have used the PEN- 3 model to design cervical cancer interventions among minority populations in the US [47]. We will also use principles from social learning to guide our participatory learning communities [45]. Social learning theory suggests that new behaviors can be supported by observing and emulating others [45]. Social learning principles have enhanced the implementation and sustainability of evidence-based interventions in real-world settings, including mother-daughter interventions [48, 49]. Finally, Proctor’s implementation outcomes framework guides the evaluation of implementation success [41]. The framework will guide our evaluation of distinct implementation outcomes (acceptability, adoption, appropriateness, cost, feasibility, fidelity, penetration, and sustainability) to determine whether success or failure was due to the intervention or the implementation process [41].

### Study setting aims and approach

#### Setting

Nigeria’s population is estimated at over 200 million, of which 49.3% are female [50, 51]. The country has 36 states mapped into six geopolitical zones with a Federal Capital territory [50]. There are also 374 distinct ethnic groups and indigenous languages spoken throughout its 36 states and Federal Capital Territory [50]. Data from the most recent Demographic Health Survey (2018) estimates that the median age at first sexual intercourse among women is 17 years of age and first marriage at 19 years [52]. Nearly half of women aged 25–49 give birth for the first time before age 21, while 19% of teenage women aged 15–19 have begun childbearing [52]. The Literacy rate in Nigeria is 60% [53]. Also, 65% of women aged 15–49 are employed or self-employed [52], while the monthly minimum wage is 30,000 naira ($18.4) [54]. Although HPV vaccine coverage has increased with the nationwide rollout at 75% [55], it remains notably below the 90% target needed to eliminate cervical cancer as a public health concern. Additionally, despite recommendations for routine cervical cancer screening for women aged 30–49, cervical cancer screening coverage remains under 10% [56, 57]. HPV self-sampling, a potentially accessible method for increasing screening uptake, is also not yet widely implemented or routinely practiced in Nigeria. Organized cervical cancer screening programs are limited, particularly in community settings where most individuals receive healthcare. Our partnership with the Nigerian Institute for Medical Research is critical for enhancing the feasibility of the study. As the key research hub within the Nigerian Ministry of Health, NIMR is well-positioned to design and deliver the intervention across the 18 recruited local government areas within the six geopolitical zones of Nigeria (See Fig. 1).

**Fig. 1 Fig1:**
[figure not shown]
Map of Nigeria and 4GW study sites

### Participants

Our stepped-wedge cluster-randomized trial will consist of two types of participants: 1) mother-daughter dyads recruited from 18 randomly selected LGAs across six geo-political zones in Nigeria with access to NIMR-affiliated clinical staff and 2) CHWs (one per LGA) and supervisors (one per LGA) implementing the intervention. Study eligibility criteria are described in Table 1.

**Table 1 Tab1:** Inclusion and exclusion criteria

Inclusion criteria (mother-daughter dyads)	• Both the mothers'/caregivers’ (between ages 30–49 years) and daughters'(Between 9 to 14 years) willingness to participate in the study• All participants must agree to informed consent in English or Pidgin English, Nigeria's second most common language.• Parental or guardian’s cell phone number for follow-up
Exclusion criteria (mother-daughter dyads)	• Inability to comply with the study protocol • Girls with recent vaccination for HPV or mothers recently screened for cervical cancer (within the last 5 years) • Illness, cognitive impairment, or threatening behaviour with acute risk to self or others

### Evidence-based intervention

We operationalize our evidence-based intervention as HPV vaccination for girls aged 9–14 and HPV screening for women aged 30–49, following national guidelines. Although these guidelines support the promotion of HPV vaccination and screening as evidence-based practices, they remain poorly implemented in routine community settings in Nigeria [27, 28]. Despite nationwide rollout, HPV vaccination uptake among adolescents falls short of the global target of 90% coverage by 2030. Similarly, organized national screening programs are lacking, limiting screening access among women [3]. While mother-daughter interventions promoting vaccination for young girls and screening for their mothers are feasible and effective in other contexts, they are underutilized in Nigeria [16]. By focusing on vaccination and screening, this study aims to enhance dyadic uptake of HPV prevention strategies to reduce cervical cancer. Additionally, we will examine barriers to dyadic participation, recognizing that service delivery points for vaccination and screening are often separate, which may impact uptake. Addressing these barriers is crucial for developing effective, community-centered HPV prevention interventions for girls and women.

#### Crowdsourced implementation strategy bundle

We will deploy a 5-component bundle, crowdsourced and designed by mother-daughter teams and pilot-tested by trained research facilitators (see Additional file 1). Our combined HPV campaign was developed through an iterative, multi-step process [36, 58], including a crowdsourcing open call, a 48-h designathon, an innovation bootcamp, and pilot-testing of seven team ideas in Nigeria. Four teams participated in Phase 1 of the nationwide rollout of HPV vaccination, where their interventions were implemented to coincide with free access to single-dose HPV vaccinations, while three teams participated in Phase 2 of the nationwide rollout of free HPV vaccination for girls. Our final crowdsourced implementation strategy bundle combines elements from the top pilot campaign in Phase 1 and Phase 2 to create the 4GW mother-daughter campaign that includes:Tailor and adapt plans to context: Mother-Daughter Day campaigns will be tailored and adapted to the local contexts within the 18 LGA with our simplified PLAN [59] building block tool used as a guide to document and track adaptations made across the 18 sites and reported using FRAME-IS after intervention.Develop partnerships: We will identify and train supervisors at NIMR-affiliated clinical sites for leadership roles and identify and prepare CHWs (1 per LGA) to build a 4GW Mother-Daughter Day coalition for cervical cancer control. Supervisors selected will be trained physicians who can provide cervical cancer treatment for mothers who test positive. Supervisors will also identify CHWs with experience conducting community health research and intentions to remain in the community for at least 12 months. A 4GW ambassador group of community research facilitators from the pilot test will support local adaptation and implementation.Capacity strengthening: We will develop and distribute educational materials for the mother-daughter Day HPV campaign, conduct ongoing training and outreach visits, and create a monthly participatory learning collaborative to reflect and document implementation phenomena periodically.Engage mothers and daughters with onsite access to services: We have previously involved mothers and daughters as teams in developing and pilot-testing the final HPV campaign. We will continue to prepare them to be active participants throughout the implementation process of the onsite services for HPV (i.e. access to study nurses for HPV vaccinations and HPV self-collection in a private area), conducting pre-post surveys that explore their perceptions of the campaigns, hurdles and opportunities for using the campaigns to increase uptake of cervical cancer prevention services among mother-daughter dyads in Nigeria.Use of evaluative and iterative strategies: Before implementation, we will assess readiness among supervisors and research facilitators to identify barriers and facilitators with implementation. We will develop and implement tools for quality monitoring and use findings to finalize an implementation blueprint for mother-daughter HPV campaigns for cervical cancer control in Nigeria.

Table 2 describes the implementation bundle using Proctor’s and colleagues’ reporting recommendations [60].

**Table 2 Tab2:** Implementation strategy specification

Domain	Strategy: 4GW Mother-Daughter Day HPV campaign
Actor	- Mother-daughter dyads, CHWs, and supervisors
Action	- Tailor and adapt the Mother-Daughter Day HPV campaign - Develop partner interrelationships for implementation - Train and educate partners - Engage mothers and daughters with onsite access to HPV services - Use evaluative and iterative strategies
Target action	- Identifying and recruiting mother-daughter dyads to the 4GW Mother-Daughter - Day HPV campaign to increase uptake of HPV vaccination for girls and HPV screening for women
Temporality	- Within 6 months of trial enrollment, HPV vaccination and HPV screening uptake will be assessed
Dose	- Time of intervention: 3 months, 6 months
Implementation outcomes	- Implementation acceptability, appropriateness, feasibility, cost, fidelity, penetration and sustainment

#### Recruitment

We will enroll mother-daughter dyads in the 18 LGAS. Recruitment methods include in-person events and venue-based, participant referral, community, religious setting and school-based referrals, social media, and online referrals. First, mother-daughter dyads will be identified and recruited to participate in an upcoming Mother-Daughter Day event on HPV prevention methods. Second, those who agree to participate will receive reminder text messages before the event. Third, trained CHWs and supervisors will provide educational information and materials on cervical cancer control at the event.

Fourth, onsite services for HPV vaccination and self-collection kits will be offered to mother-daughter dyads, with girls receiving HPV vaccinations immediately in an onsite vaccination dedicated private space designated for the mother-daughter Day event. Mothers will receive instructions on self-collection in a private area, and their samples will be returned to the NIMR laboratory. Trained CHWs will provide the results of the samples, and those with positive results will be linked immediately to the supervisors for treatment and follow-up care, which we will track overtime. A baseline survey will be conducted among 612 mother/daughter dyads (*n* = 1,224 total) recruited in 18 LGAs (capped at 34 per area). We will define mothers as any female caregiver, including biological and surrogate mothers or close relatives who meet eligibility criteria. Eligibility criteria for mother-daughter dyads are outlined in Table 1. Trained community healthcare workers will approach and obtain consent from participants in a private space. Parental mobile phone numbers will be collected as tracking information for follow-up and retention.

#### Randomization and rationale for stepped-wedge design

The 18 LGAs will be randomly allocated to the intervention, 4–5 LGAs per month for 12 months. All sites begin as part of the control condition and are block-randomized into four waves, with each wave beginning two months after the start of the prior wave and lasting for 6 months, followed by a 6-month follow-up period. All clusters will eventually receive the intervention, with outcomes measured every three months across all clusters. See Fig. 2for a schematic of the stepped-wedge cluster RCT design. Randomization will be conducted by the study statistician, who will not have direct contact with the LGAs. All LGAs will be informed of their assigned intervention wave before the first wave begins. Blinding was not implemented in this study, as all sites will eventually receive intervention, reflecting typical conditions in real-world settings. The stepped-wedge design was deemed acceptable and ethical by key program partners (NIMR and the Nigerian Ministry of Health) and study collaborators for logistical and pragmatic reasons, given the potential benefits of the intervention package (i.e., combined cervical cancer prevention strategies of vaccination and screening) and the equitable provision of the intervention to all sites [40].

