#### Sample size and power considerations

We performed an a priori power analysis to determine the sufficient sample size for the stepped-wedge cluster RCT design, where the unit of randomization is the geographic area (cluster). Thus, there are two important sample estimates: N, for the number of mother/daughter dyads and K, for the number of LGAs. Specifically, the N participants will be nested within the K clusters. This nesting will likely create dependency on the data. The degree of this dependency depends on the intraclass correlation coefficient (ICC). The required sample size is calculated for the primary outcomes of HPV vaccination uptake for daughters and HPV self-collection uptake for mothers. Assuming a total of 18 LGAs with 34 dyads per LGA (N1 = 18 × 34 = 612 for daughters and N2 = 18 × 34 = 612 for mothers, total N = N1 + N2 = 1224), four total intervention periods, 2-sided alpha = 0.05 and 80% power, we calculated the minimum detectable rate of the primary outcome uptake at follow-up (Table 3 below). We expect three possible baseline rates of 0.10, 0.15, and 0.20 and compute the minimum detectable differences between the baseline and follow-up rates (hence minimum detectable follow-up rates) for the two primary study outcomes, assuming three possible ICC values of 0.005, 0.01, and 0.05. As shown in Table 1, the minimally detectable follow-up rates are much less than expected of the follow-up 50–60% self-collection uptake rates [67–69] and 65% HPV vaccination [11]. Hence, we have sufficient power (> 80%) to detect the increases in HPV vaccination among girls and HPV self-collection among their mothers after the implementation of the final crowdsourced campaign with a total of 18 clusters with 34 dyads per cluster (Table 3). To account for the 15% attrition rate at 6 months follow-up, we increased the sample size to 704 for mothers and daughters (40 dyads for each cluster). The calculation was performed using the software PASS 2019 (Power Analysis and Sample Size Software (2019) with the formulas developed by Hussey et al. [70]

**Table 3 Tab3:** Power and sample size for stepped-wedge RCT^a^

Cluster size (total sample size)	Rate of primary outcome at baseline (HPV self-collection uptake for mothers, HPV vaccination for daughters)								
	0.10^a^			^a^0.15			^a^0.20		
	ICC			ICC			ICC		
	0.005	0.01	0.05	0.005	0.01	0.05	0.005	0.01	0.05

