### Statistical analysis

#### Data analysis

The primary analyses will examine rates of HPV self-collection (mothers) and single-dose vaccine receipt (daughters). Analyses will be performed separately for the mother sample and daughter samples. The main analyses will compare the rates of HPV self-collection (mothers) and vaccine uptake during the pre-and post-intervention periods. We will examine a hypothesis comparing the superiority of the intervention with pre-intervention periods using the stepped-wedge cluster randomized control design and account for any temporal changes in HPV vaccination or screening rates during the 6-month conduct of the trial. This analysis will be accomplished with generalized linear mixed models to account for the within-person factor – time (baseline, 3 months, and 6 months) and one primary between-person factor (randomization site dummy code as 0 = convention and 1 = intervention). The 3-level model is structured as observations nested within subjects within local government areas. Multilevel modeling software (SAS, version 9.4, PROC GLIMMIX with logit as link function) will be used to compute full information maximum likelihood (FIML) estimates of the model parameters. The model will include intervention status and time as fixed effects and site and individuals as random effects. The estimated intervention effects will be reported with 95% CIs and p values. Secondary analyses will explore linkage rates to clinical follow-up after positive HPV testing in pre-intervention and post-intervention periods.

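### The roll-out calendar contradicts itself, a common three-monthly grid cannot separate four waves starting two months apart, and Table 3 is computed for a step grid that the measurement and model schedule does not supply

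*Protocol article*

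**What the plan says.** The section on randomization and the stepped-wedge rationale gives the roll-out twice. First: "The 18 LGAs will be randomly allocated to the intervention, 4–5 LGAs per month for 12 months". Then the LGAs are "block-randomized into four waves, with each wave beginning two months after the start of the prior wave and lasting for 6 months", followed by six months of follow-up. The same paragraph has all clusters assessed together, "with outcomes measured every three months across all clusters".

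The sample size section powers the trial on 18 LGAs of 34 dyads with "four total intervention periods, 2-sided alpha = 0.05 and 80% power", using the Hussey-Hughes formulas.

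The data analysis section fits a mixed model with a within-person factor, "time (baseline, 3 months, and 6 months". It promises to account for temporal change in uptake "during the 6-month conduct of the trial". Table 4 lists uptake at the same three time points. The Methods section adds: "All mother-daughter dyads will be followed for 12 months".

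**The concern.** A stepped-wedge trial separates the campaign effect from secular trend only through the grid of randomised start times against calendar periods. Here that grid is not fixed. The roll-out rate is given in two incompatible ways, the measurement interval is longer than the step interval, and the model's time points stop at 6 months. Under the four-wave sentence, the last wave does not finish its intervention until 12 months after the first wave starts.

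Trend matters in this trial. The Introduction describes a national vaccination roll-out launched in October 2023 and extended in May 2024, and the analysis section undertakes to account for temporal change. If waves merge, or if the time factor is not calendar period, part of the randomised information that supports this adjustment is lost. The figures in Table 3 then describe a different design.

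**Working it through.** **Calendar.** 18/4 = 4.5 LGAs per wave, so 4 to 5 is a wave size. At 4 to 5 LGAs per month, 18 LGAs would be used up in about four months. Four waves two months apart have starts spanning six months, and with six months each the last wave ends at month 6 + 6 = 12. The 12 months in the first sentence therefore agrees with the four-wave calendar. The monthly rate does not, and nor does the six-month trial in the analysis section if that means calendar time.

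**Can a three-monthly grid separate the waves?** Let starts be s, s+2, s+4 and s+6. Separating all four needs one measurement in each of three consecutive two-month gaps. If the first is at t ≥ s, the third is at t+6 ≥ s+6, which is past the last gap. So two waves always share a sequence:

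| Wave starts (months) | First measured as exposed | Merged pair |
|---|---|---|
| 0, 2, 4, 6 | 3, 3, 6, 9 | first two |
| 1.5, 3.5, 5.5, 7.5 | 3, 6, 6, 9 | middle two |
| 2.5, 4.5, 6.5, 8.5 | 3, 6, 9, 9 | last two |

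Offsets from 0 to 3 months in quarter-month steps all gave exactly three distinct sequences.

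**Reproducing Table 3.** The Hussey-Hughes variance is

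Var = Iσ²(σ² + Tτ²) / [(IU − W)σ² + (U² + ITU − TW − IV)τ²]

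Here I is the number of clusters and T the number of periods. U is the number of exposed cluster-periods, W the sum of squared period totals and V the sum of squared cluster totals. σ² = v/m with m dyads per cluster-period, v is the mean of the two binomial variances, and τ² = v·ICC/(1 − ICC).

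Four sequences (5, 4, 5, 4 LGAs), T = 5, with 34/5 = 6.8 rounded to 7 dyads per cluster-period:
- U = 46, W = 626, V = 140.
- For 0.10 against 0.220 at ICC 0.01: v = (0.09 + 0.1716)/2 = 0.1308, σ² = 0.01869, τ² = 0.00132.
- Var = 0.001859, SE 0.0431, power = Φ(0.12/0.0431 − 1.96) ≈ 0.795.
- The minimum detectable rate is 0.221, against 0.220 stated.

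All nine entries are reproduced within 0.0016, with power of 79.1–80.3% at the stated rates. Of the readings tried that keep 34 dyads per cluster, only this one matched.

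**Quarterly grid (0, 3, 6, 9 months), 34 dyads kept, so 34/4 = 8.5 per period (σ² = 0.01539).**
- End pair merged (9, 4, 5 LGAs): U = 40, W = 574, V = 102. Var = 0.002116, power at 0.220 is 0.742, minimum detectable rate 0.230.
- Middle pair merged (5, 9, 4 LGAs): U = 37, W = 545, V = 85. Var = 0.002502, power at 0.220 is 0.670, minimum detectable rate 0.243.

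**Grid of 0, 3, 6 months, 34/3 dyads per period.** With an end pair merged, the minimum detectable rate is 0.213–0.217, which is no loss against Table 3.

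**Expected effects.** From 0.20 to 0.50, power is at least 98% in every variant, including ICC 0.05.

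**The model's clock.**
- If baseline, 3 and 6 months run from the first wave, the last wave starts at month 6 or later and contributes little or no exposed data.
- If they run from enrolment, and LGAs enrol at different dates, the listed time factor is not calendar period. Nothing in the stated model then removes the secular trend.
- If all LGAs enrol together, the two clocks coincide and the first problem applies.

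**The case against.** Several parts of the opposing case are sound, and they limit the point.

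- **Roll-out arithmetic.** A reader could multiply 4 to 5 by 12 and report 48 to 60 LGA starts. That is uncharitable: the count plainly describes a wave, and 12 months fits the four-wave calendar. The conflict lies in the monthly rate alone.
- **Size of the loss.** A reader might infer a variance increase of 36–46% and detectable rates of 0.246–0.252. Those figures come from holding 6.8 dyads per assessment while dropping periods, which cuts each LGA from 34 dyads to 4 × 6.8 = 27.2 or 3 × 6.8 = 20.4. With 34 kept, the quarterly loss is smaller and the 0/3/6 loss disappears. If all 34 dyads contribute in every period, power at the Table 3 rates exceeds 99%.
- **Last wave never seen on intervention.** This holds only on a calendar clock from the first wave. The article calls time a within-person factor, defines uptake within six months of enrolment and follows dyads for 12 months, which suggests a participant clock. On that clock the last wave is observed on intervention, but the time factor is then no longer calendar period.
- **Misclassified exposure.** It is tempting to say that part-exposed periods are counted as fully exposed. The article states no coding rule, and such a rule may properly sit in the analysis plan.
- **Irretrievable loss.** The primary events come from clinical records and laboratory receipt. If these are dated, the steps can be recovered.

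Fig. 2, the design schematic, was not available for this check. Even if it shows a coherent grid, the sentences still conflict with each other.

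**Conclusion.** The point holds in a limited form. The two roll-out statements are incompatible. A common three-monthly calendar grid leaves three measured sequences, not four. Table 3 rests on a four-step, five-period layout. The model's time points, on either clock, do not deliver the calendar-period adjustment that a stepped-wedge analysis depends on.

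The cost in precision is modest: at baseline 0.10 and ICC 0.01, a rise of about 0.01 to 0.02 in the detectable rate and a fall in power at the Table 3 rate from about 80% to 67–74%. This assumes that measurement falls on one calendar grid and that 34 dyads per LGA are spread evenly over four periods. It does not show the trial to be underpowered for the 50–65% uptake that the sponsor expects. The stronger reason to act is the separation of campaign effect from trend, which the text leaves unsecured.

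**What to change.** 1. Reconcile the roll-out sentences, and Fig. 2 if needed, to one step interval with 4 to 5 LGAs per wave. LGAs are to be told their wave before the first one begins, so this should be settled by then.
2. Define calendar periods that match that interval for the primary outcomes, using dates of vaccination and specimen receipt. This assumes that the records carry dates; if so, no visits are added. The three-monthly surveys can stay as they are.
3. State which clock the model uses, and fit calendar period as the time effect through the last wave's intervention period.
4. Say how uptake within six months of enrolment maps to those periods. If the mapping alters the primary endpoint, declare it as a change to the endpoint.
5. Recompute Table 3 on that grid.

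The cost is protocol wording, some rework of the analysis specification and one rerun of the power calculation, with possibly slightly less favourable figures in Table 3.
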